| 
Brazil
 
For evaluations of experimental interventions compared to control, a total of 492 persons per arm will be enrolled.
 
A second cohort of low-risk participants will not be enrolled in Brazil.
                                                                                                                                                                                                                                                                                                                                                                                                                                                                                                                                                                                                                                                                                                                                                                                                                                                                                                                                                                                                                                                                                                                                                                                                                                                                                                                                                                                                                                                                                                                                                                                                           |

|                                          |                 |
|------------------------------------------|-----------------|
| Date/version: May 19, 2020 – V1.0 | Page: 10 |
|------------------------------------------|-----------------|

| Harmonized protocol document                                                          |
|---------------------------------------------------------------------------------------|
| Short title: Outpatient Management of SARS-CoV-2 for High-Risk Adults in LMICs |

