**Sample size:**

In Brazil, 492 patients per arm for placebo, HCQ, and LPV/r to achieve 90% power with 0.05 two-sided Type 1 error for a pairwise comparison against the control (ascorbic acid) to detect minimum treatment efficacy defined by 27.5 % relative risk reduction (RRR) of preventing hospitalization assuming a control event rate (CER) of 20%. Eligible participants will be randomized at an equal allocation ratio to study experimental interventions or placebo. In Brazil, if other eligible patient(s) are in the same household, they may be assigned to different regimen.

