### **5.1.1. Study Execution for Brazil**

This study will be carried in two stages: *Internal Pilot and Main Stages*

Due to the rapid evolution of the COVID-19 pandemic and the challenge that public health systems will face to respond to this devastating infection, there are several aspects related to the feasibility of the study that need to be evaluated as soon as we start implementing it.

The aim of the internal pilot phase is to assess any unpredictable feasibility problems and resolve them to improve the overall success of the research. In particular, we will assess issues related to drug recruitment, consent, availability and administration, data collection and recording. This will involve about 18-20 patients in total. There will be no statistical analysis at the end of the pilot stage. The pilot and main stages will be operationally connected with the patients enrolled in the pilot stage will be transferred to the main stage during which the recruitment efforts will be amplified.

The pilot stage will start with two arms: HCQ and placebo, with LPV/r possibly being added if the drug supply becomes available during the pilot stage.

The main stage will begin with three arms: HCQ, LPV/r, and placebo. Safety profile of the monotherapy arms will be tested after being administered for 100 patients per arm. This will be reviewed internally and externally with AbbVie. If adequate safety profile is observed in both monotherapies, combined arm of HCQ + LPV/r will be added into the TOGETHER 2 with permission from AbbVie.

With the time required to review the safety profile of HCQ and LPV/r monotherapy with AbbVie, (assuming adequate safety profile) the fourth arm of combined HCQ + LPV/r will likely be introduced into the trial after enrolment of 165 per arm has already been randomized to the three initial groups of placebo, HCQ, and LPV/r.

For the clinical evaluation of HCQ + LPV/r arm versus placebo, we will use unequal allocation of 3:1 (165 for combined arm and additional 55 for placebo arm) and will incorporate the previously placebo control data by borrowing the individual treatment effects of HCQ and LPV/r versus placebo as empirical prior for the clinical evaluation of the combined arm.

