### **5.2. Participant and Study Completion**

As an initial target, up to 165 high risk participants per arm will be randomly assigned to study treatment or control in Brazil. There may be more than 165 patients randomized to the placebo arm during the entire duration of the trial given the possible addition of HCQ+LPV/r arm.

This sample size target will likely increase based on the blinded sample size re-assessment.

|                                          |                 |
|------------------------------------------|-----------------|
| Date/version: May 19, 2020 – V1.0 | Page: 24 |
|------------------------------------------|-----------------|

| Harmonized protocol document                                                          |
|---------------------------------------------------------------------------------------|
| Short title: Outpatient Management of SARS-CoV-2 for High-Risk Adults in LMICs |

A participant is considered to have completed the study if he/she has completed all phases of the study including the last scheduled procedure shown in the Schedule of Activities (SoA). The clinical evaluation of each experimental intervention will be considered completed when sufficient number of participants complete the study to enable appropriate evaluation of the primary endpoint.

| Harmonized protocol document                                                          |
|---------------------------------------------------------------------------------------|
| Short title: Outpatient Management of SARS-CoV-2 for High-Risk Adults in LMICs |

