## **12. Statistical Considerations**

### **12.1. Sample Size Determination for Brazil**

The sample size for Brazil of 492 patients per arm has been chosen for each experimental group to achieve 90% power with 0.05 two-sided Type 1 error for a pairwise comparison against the control (ascorbic acid) to detect minimum treatment efficacy defined by 27.5 % relative risk reduction (RRR) of preventing hospitalization assuming a control event rate (CER) of 20%.

The table below shows the sample size required at various treatment effects, CER, and drop-out rates for operating characteristics of 90% statistical power and two-sided type I error rate of 5%. Power may be lower depending on CER and drop-out rate (Table 1). As the initial sample size target, 165 per arm has been initially chosen for each experimental group to achieve 90% power with 0.05 two-sided Type 1 error for a pairwise comparison against the control (ascorbic acid) to detect at least 50% treatment efficacy in reducing the progression to LRTI (primary endpoint) assuming a CER of 30% and 5% drop-out rate.

**Table 1 Sample Size Per Arm Required to Detect a Relative Risk Reduction of 40% to 60% Under Various Control Event and Drop-out Rates**

| RR
R | Drop-out rate = 0% |             |             | Drop-out rate = 5% |             |             | Drop-out rate = 20% |             |             |
|---------|--------------------|-------------|-------------|--------------------|-------------|-------------|---------------------|-------------|-------------|
|         | CER=1
0%        | CER=2
0% | CER=3
0% | CER=1
0%        | CER=2
0% | CER=3
0% | CER=1
0%         | CER=2
0% | CER=3
0% |
| 40
% | 962                | 437         | 261         | 1013               | 460         | 275         | 1202                | 546         | 327         |
| 50
% | 578                | 263         | 158         | 609                | 277         | 165  | 723                 | 329         | 198         |
| 60
% | 375                | 171         | 103         | 395                | 180         | 108         | 469                 | 214         | 128         |

**Acronyms:** CER: Control event rate; RRR: Relative risk reduction.

Sample size calculation was done with the desired operating characteristics of 90% statistical power and 5% type I error rate (two-sided).

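### The HCQ + LPV/r evaluation keeps a 165 + 55 size inherited from the LRTI calculation; a direct comparison on hospitalisation has about 15–40% power, and the arm's size conflicts with the 492-per-arm, 90% statement

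*Protocol*

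**What the plan says.** Protocol 5.1.1 (Study Execution for Brazil) plans a fourth arm, HCQ + LPV/r, if the monotherapies show adequate safety and the drug company agrees. It expects the arm to open after about 165 patients per arm have been randomised to placebo, HCQ and LPV/r. For the combination against placebo, "we will use unequal allocation of 3:1 (165 for combined arm and additional 55 for placebo arm"). The same sentence adds the earlier placebo data and uses the HCQ and LPV/r effects versus placebo as an empirical prior. It gives no weight for that prior.

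Section 5.2 treats 165 as the base size: "There may be more than 165 patients randomized to the placebo arm during the entire duration of the trial", because the combination arm may be added. It also says the target will probably rise after the blinded re-assessment.

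Other places give a different size:
- Section 12.1: "492 patients per arm has been chosen for each experimental group to achieve 90% power with 0.05 two-sided Type 1 error", for a 27.5% relative risk reduction in hospitalisation at a 20% control rate.
- Synopsis, Population table: "For evaluations of experimental interventions compared to control, a total of 492 persons per arm will be enrolled".
- Synopsis, Sample size: "492 patients per arm for placebo, HCQ, and LPV/r to achieve 90% power". The combination is not named.
- Section 5.1: 492 per arm for the Brazil study.

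Section 12.1 also gives the source of 165: LRTI, 50% reduction, 30% control rate, 5% drop-out, equal arms. Section 12.3.1 has the primary analysis use all placebo patients, concurrent or not, through an empirical Bayesian borrowing method. No section states a power for the combination arm.

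**The concern.** Section 4.1 makes hospitalisation (or clinical worsening) and COVID-19 mortality primary, and LRTI secondary. The headline sample size moved to a hospitalisation calculation, but 5.1.1 and 5.2 kept the LRTI number. That number was derived for equal allocation and is applied at 3:1 without being recalculated.

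Two things are at stake. First, a patient-level comparison of two drugs given together could be run with little chance of detecting the hospitalisation effect the trial is designed for, and readers could not tell from the protocol what a null result would mean. Second, the placebo count is unclear. If placebo continues to 492, another 492 − 165 = 327 placebo patients follow the opening of the new arm. The text does not say whether the 55 are among those or on top of them.

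**Working it through.** **Inputs.** Hospitalisation: p0 = 0.20, p1 = 0.20 × (1 − 0.275) = 0.145, difference d = 0.055 (12.1). LRTI: p0 = 0.30, p1 = 0.15, d = 0.15 (12.1). Two-sided alpha 0.05. Combination arm n1 = 165. Placebo n0 is 55 (concurrent only), 165 + 55 = 220 (5.1.1), or 492 + 55 = 547 (assumption: placebo reaches 492 and the 55 are extra).

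**Reproducing the plan's figures.** Unpooled formula: n per arm = (1.960 + 1.282)² × [p0(1−p0) + p1(1−p1)] / d². This gives every 0% drop-out cell of Table 1: 962/437/261, 578/263/158 and 375/171/103. For LRTI, 157.6 / 0.95 = 165.9, which accounts for the 165.

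For hospitalisation the same formula gives 10.507 × (0.1600 + 0.1240) / 0.003025 = 986.4, so 987 per arm (990 with pooled variance). The stated 492 is about half of that. With 492 per arm, SE = √(0.1600/492 + 0.1240/492) = 0.02402, d/SE = 2.289, and power = Φ(2.289 − 1.960) = 63%.

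**Combination arm, direct comparison on hospitalisation.** Unpooled: SE = √(p0(1−p0)/n0 + p1(1−p1)/n1), power ≈ Φ(d/SE − 1.960) plus the negligible opposite tail. The pooled version puts the pooled-variance SE in the critical value.

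| Placebo n0 | Unpooled SE | Unpooled power | Pooled power |
|---|---|---|---|
| 55 | 0.0605 | 14.9% | 17.5–17.8% |
| 220 | 0.0385 | 29.9% | 28.4% |
| 547 | 0.0323 | 39.8% | 34.5% |
| unlimited | 0.0274 | 51.9% | 41.3% |

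Simulation of 200,000 trials per case with the pooled test gave about 17.5%, 28.5% and 35.1% for the first three rows. With 5% drop-out the pooled figures fall to 16.9%, 27.2% and 32.9%. The last row matters most: the 165 treated patients cap the power, so borrowing placebo patients alone cannot bring it near 90%.

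The relative reduction detectable with 90% power is about 78–89% with 55 controls, 56–58% with 220 and 48–52% with 547, against the 27.5% target.

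**LRTI with the same arm.** 165 vs 55: 60% (unpooled) to 68% (pooled). 165 vs 220: 95% to 94%. Solving the unpooled formula for 90% gives about 154 effective controls, so past placebo would need a weight of about (154 − 55)/165 = 0.60.

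**Bound on the monotherapy prior.** Assume both monotherapies truly have the 27.5% reduction and are pooled at full weight with the combination. With 165 per monotherapy arm, 165 × 3 = 495 treated vs 220 placebo gives about 42% (unpooled) to 46% (pooled). With 492 per monotherapy arm, 165 + 984 = 1,149 treated vs 547 placebo gives about 78% to 81%. Neither reaches 90%.

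**The case against.** The strongest reply is that the protocol never states 90% for the combination. A reader might infer that it does from the wording in 12.1 about each experimental group and from the Synopsis Population table. The Synopsis sample-size paragraph, however, ties 492 and 90% to placebo, HCQ and LPV/r; the Population table gives no power; and the arm is conditional. This stands: the text is ambiguous about whether 90% covers this arm, and it should not be read as a clear promise.

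A reader might also infer that the arm's power is fixed at 15–30% as written. That is not supported either. Section 5.1.1 adds a prior from the monotherapy effects, 12.3.1 uses all placebo patients, and 12.3.1 leaves the technical details of borrowing to the SAP. The weight is unknown, so only the power of a direct comparison can be computed, and calling 30% the full-borrowing figure would be wrong.

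On LRTI the inherited size is adequate under the planned analysis. Section 4.1 says the trial was initially powered for LRTI, and about 60% weight on the earlier placebo patients is enough. Full weight is not required.

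Finally, 5.2 calls 165 an initial target likely to rise, and 5.1 has the DSMB review proposed size changes and advise on allocation. This makes 165 provisional but does not cure the mismatch: the re-assessment responds to control event rate and drop-out, and nothing in it changes the endpoint or the effect size or recalculates for 3:1.

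**Conclusion.** The inconsistency is real. The 165/55 figures in 5.1.1, and 165 as the placebo base in 5.2, are left over from the LRTI sizing and do not fit 492 per arm or a hospitalisation endpoint. In a direct comparison on hospitalisation the arm has about 15–18% power with 55 concurrent controls, 28–30% with 220 and 34–40% with 547. The ceiling is 41–52% from placebo data alone. These figures rest on 20% vs 14.5%, two-sided 5%, no drop-out, and placebo counted at full weight. Any gain from the monotherapy prior comes on top and cannot be quantified from the protocol; under the favourable bounds examined it still falls short of 90%.

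The 90% benchmark does not hold even for the main arms, where 492 per arm gives about 63%. The point should be fixed but does not block the trial, since the arm is conditional and its size is described as initial.

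**What to change.** 1. In 5.1.1 and 5.2, reconcile 165 and 55 with the hospitalisation endpoint and with 492 per arm. Say whether the 55 placebo patients are part of the 492 or additional to them.
2. State the combination arm's hospitalisation power for a direct comparison: about 15–18% with 55 controls, 28–30% with 220, 34–40% with all placebo. Report any gain from the monotherapy prior separately, with its weight and the assumed monotherapy effects.
3. If 165 + 55 is kept, label that evaluation exploratory for hospitalisation.
4. In 12.1, limit the 90% statement so that it does not cover this arm.
5. Restate the benchmark in 12.1 and the Synopsis: about 63% power at 492 per arm, or about 987 per arm for 90%.

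The cost is protocol wording and less favourable stated power. No extra patients are needed if the figures are restated. Resizing the combination for 90% on hospitalisation by direct comparison would be a different matter: about 990 per arm at 1:1, or about 1,950 versus 650 at 3:1.

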A blinded sample size re-assessment will be done to potentially increase the sample size target during the trial, should a lower control event rate (CER) and/or higher drop-out rate be observed. The decision on the timing of the sample size re-assessment will be made by the independent DSMB during the trial based on the observed recruitment rate. The DSMB will also decide on a possible interim analysis during the trial after the sample size re-assessment based on the information on the observed recruitment rate, the CER, the drop-out rate, and the final sample size target, if applicable.

The decision for interim analysis will be made in a blinded manner (e.g., based on pooled number of events). The interim monitoring plan (written by the Study Statistician) will define monitoring bounds to maintain the two-sided type I error rate at the desired 5% (e.g. 97.5% or higher

| Harmonized protocol document                                                          |
|---------------------------------------------------------------------------------------|
| Short title: Outpatient Management of SARS-CoV-2 for High-Risk Adults in LMICs |

probability of superiority over the control group). Should a new experimental candidate be added during the trial, allocation ratios will be adapted to favor the new arm.

If additional data emerge on alternative potentially effective agents for SARS-CoV-2, additional arms can be added to the study as a new intervention appendix to the protocol. The standardized operating procedures and comprehensive statistical analysis plans will allow for integration of new arms.

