#### **Empirical Bayesian information borrowing method:**

In the case that a new experimental treatment is added into this platform trial, there will already be data collected from patients who are enrolled prior (past data). To incorporate the past control data with the concurrent control data from patients who are concurrently enrolled, empirical Bayesian information borrowing method will be used. Instead of using concurrent data only, combining past data with the concurrent data can potentially be advantageous in terms of statistical power and lower number of participants that are needed to be randomized to the control arm. This is particularly important for possible improved ethics and feasibility for the context of conducting a platform trial for SARS-CoV-2. Additionally, in the case that relevant external trial data become available, this empirical information borrowing method may be used. The DSMB, which will contain clinical experts, will make on whether to include or ignore the external trial data. The Study Statistician will assess the similarities of the external trial(s) to this clinical trial in terms of eligibility criteria, trial location, data collection procedures, and the reliability and comprehensiveness of the available dataset. If deemed appropriate, the empirical Bayesian information borrowing method will be used to determine the degree of the information that can be “borrowed” from the external dataset and be used for the statistical comparison.

As there are multiple randomized clinical trials that are either ongoing or being planned right now for SARS-CoV-2 with potentially relevant interventions, it is important to plan for an approach, such as this empirical Bayesian borrowing method, that can potentially incorporate these external data with the internal data. An important feature of this method is the avoidance of use of any subjective or informative prior distributions that may become a point of dispute in certain schools of thought.

|                                          |                 |
|------------------------------------------|-----------------|
| Date/version: May 19, 2020 – V1.0 | Page: 48 |
|------------------------------------------|-----------------|

The full technical details on the empirical Bayesian information borrowing method will be described in the Statistical Analysis Plan.

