#### **Interim Analysis:**

The DSMB will decide on a possible interim analysis during the trial after the sample size re-assessment based on the information on the observed recruitment rate, the CER, the drop-out rate, and the final sample size target, if applicable. The decision for interim analysis will be made in a blinded manner (e.g., based on pooled number of events). The interim monitoring plan (written by the Study Statistician) will define monitoring bounds to maintain the two-sided type I error rate at the desired 5% (e.g. 97.5% or higher probability of superiority over the control group). Should new experimental candidates be added during the trial, allocation ratios will be adapted to favor the new arms.

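### Section 5.1.1 puts the HCQ and LPV/r treatment effects into the prior for HCQ+LPV/r versus placebo, which biases the test of the combination and does not fit the borrowing method of section 12.3.1

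*Protocol*

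**What the plan says.** Protocol section 5.1.1 (Study Execution for Brazil) provides for a fourth arm, HCQ+LPV/r, after a safety review of the single drugs and an external company's permission. It expects the arm to open "after enrolment of 165 per arm has already been randomized to the three initial groups of placebo, HCQ, and LPV/r". For HCQ+LPV/r versus placebo it states: "we will use unequal allocation of 3:1 (165 for combined arm and additional 55 for placebo arm"). It then says that earlier placebo data will come in by "borrowing the individual treatment effects of HCQ and LPV/r versus placebo as empirical prior for the clinical evaluation of the combined arm".

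Section 12.3.1 describes the borrowing method in other terms. Its purpose when an arm is added is "To incorporate the past control data with the concurrent control data", and it may also be used for external trial data. It adds: "An important feature of this method is the avoidance of use of any subjective or informative prior distributions". Technical details are left to the SAP. The primary analysis paragraph of the same section likewise speaks of using all placebo participants, contemporaneous or not.

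On error control, section 5.1 asks for monitoring bounds "to maintain the two-sided type I error rate at the desired 5" per cent, and the interim analysis paragraph gives as an example "e.g. 97.5% or higher probability of superiority over the control group". Section 12.1 sizes the pairwise comparisons "to achieve 90% power with 0.05 two-sided Type 1 error".

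**The concern.** The question for the added arm is whether the combination beats placebo; the null is no effect of the combination. Borrowing earlier placebo outcomes sharpens the estimate of the control rate and says nothing about the combination. Borrowing the monotherapy effects is different: it starts the analysis from the premise that the combination does roughly what the single drugs did. The sentence in section 5.1.1 runs the two together, since it says that placebo data are brought in by borrowing treatment effects.

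The arm opens on a safety review, whatever the efficacy of the single drugs, so the prior may turn out favourable or null. A favourable one can carry a combination that does nothing, for example because the drugs interact, towards a superiority claim. A null one can hold back a combination that works only when both drugs are given.

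**Working it through.** **Inputs from the protocol.** 165 on the combination and 55 new placebo patients; 165 earlier patients on each of placebo, HCQ and LPV/r (5.1.1). Control event rate (CER) 30% with 50% relative risk reduction (RRR), behind the 165, and CER 20% with 27.5% RRR for hospitalization (12.1). Two-sided 5%, so 2.5% in the superiority direction.

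**The plan's own figure.** For 30% versus 15% at 90% power: (1.960 + 1.282)² × (0.21 + 0.1275) / 0.15² = 157.6 per arm, 158 in Table 1. Dividing by 0.95 for drop-out gives 165.9, against the stated 165. The figure reproduces.

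**Assumptions, because the protocol does not give them.** Log odds ratio scale; prior centred on the mean of the two monotherapy effects, with its sampling variance plus a discount τ²; likelihood from the combination versus the 55 new placebo patients; superiority if the posterior probability is at least 97.5%; no drop-out. The estimated discount is τ² = max(0, (d − m)² − v_d − v_m), where d is the observed combination effect, m the prior mean, and v_d and v_m their variances.

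**By hand, CER 30%, both single drugs at 15%, combination inert.**

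- Prior mean: ln(0.15/0.85) − ln(0.30/0.70) = −0.887.
- Variance of a log odds: 1/(np) + 1/(n(1 − p)). Earlier placebo 0.0289; each single-drug arm 0.0475.
- Prior variance, τ = 0: 0.0289 + (0.0475 + 0.0475)/4 = 0.0526.
- Likelihood variance: 0.0289 (combination) + 0.0866 (55 placebo) = 0.1154.
- Weight on the prior: (1/0.0526) / (1/0.0526 + 1/0.1154) = 0.69.
- Expected posterior mean: 0.69 × (−0.887) = −0.61; posterior SD 0.190; ratio −3.21.
- Chance of passing −1.96: Φ(3.21 − 1.96) = 0.89.
- With τ = 0.5 the prior weight is 0.28 and the chance 0.10. With τ = 1 they are 0.10 and 0.04.

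**Simulation, inert combination, both single drugs effective: chance of false superiority (nominal 2.5%).**

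| Analysis | CER 30%, RRR 50% | CER 20%, RRR 27.5% |
|---|---|---|
| Prior, τ = 0 | 90% | 28% |
| Prior, τ estimated | 18% | 17% |
| Prior, τ = 0.5 | about 10% | 4% |
| Prior, τ = 1 | 4% | 3% |
| No prior, 55 new placebo only | 2.7% | 2.9% |
| No prior, all 220 placebo pooled | 2.3% | about 2.3% |

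With no prior and 55 placebo patients, the normal approximation alone gives 2.7% to 2.9%. At CER 20% and τ = 1 the prior therefore adds almost nothing.

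**The other direction, CER 30%: combination at 50% RRR, both single drugs inert.** Power is about 68% from the 165 and 55 alone. It falls to 23% with the prior at τ = 0, to 53% at τ = 0.5, to 64% at τ = 1, and to 63% with τ estimated. Pooling all placebo patients without the prior gives 94%.

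**The case against.** The strongest reply is that the headline error depends on a setting the protocol leaves open. Section 12.3.1 defers technical details to the SAP and, for external data, says that the method will determine how much is borrowed, so some discount is plausible. That stands: 90% is not the error rate of this plan, only the undiscounted end of a range that runs down close to nominal. What the SAP cannot settle is the choice of what is borrowed, because section 5.1.1 has already made it.

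Stronger readings are tempting, and the documents do not support them:

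- **The combination could win on monotherapy data alone.** It could not; the 165 combination and 55 new placebo patients always enter the posterior.
- **Section 12.3.1 forbids borrowing anything but control data.** It describes control borrowing and allows external trial data, but states no such limit. The two sections are inconsistent, without an express prohibition.
- **The earlier 165 placebo patients are counted twice.** That happens only if they enter the likelihood as well as the prior. On the wording of 5.1.1 the prior may be their only route in.
- **An effective combination would usually be missed.** The loss is large only with little or no discounting; with an estimated discount it is 68% to 63% against the same placebo data.

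The arm is also conditional, and the comparisons of HCQ and of LPV/r with placebo do not use this prior. This limits the reach of the point and leaves its substance intact.

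**Conclusion.** The point holds in this form: section 5.1.1 places an informative prior on the treatment effect being tested, and that does not fit the method described in section 12.3.1. The direction of the bias follows from the text. When both single drugs work and the combination does not, false superiority rises above that of the same analysis without the prior, from severely (90% at CER 30% and 50% RRR, 28% at CER 20% and 27.5% RRR, undiscounted) to barely (4% and 3% at τ = 1). An estimated discount still leaves 18% and 17%. Nothing in the protocol shows that 5% two-sided is kept for this comparison.

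The sizes rest on the assumed form of the prior (mean of the two effects), the assumed discounts and the sample sizes of section 5.1.1. The direction does not depend on the exact discount. The loss of power is the weaker half and matters mainly under strong borrowing.

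**What to change.** Reword section 5.1.1 so that borrowing for HCQ+LPV/r versus placebo is limited to placebo-arm outcomes, with each placebo patient used once, in line with section 12.3.1, and with a non-informative prior on the combination effect. A posterior informed by the monotherapy effects may be reported as supportive, but should not by itself carry a superiority claim. Carry the same wording into the SAP, and make the change before the combined arm opens.

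The cost is wording and no extra patients. Some precision is lost when the combination and both single drugs truly share one effect: at CER 30% and 50% RRR, power goes from about 99% with the undiscounted prior to 94% with all placebo patients pooled, if the placebo event rate does not drift over time. With concurrent placebo only it is about 68%. Against a prior with an estimated discount (93% in the same case), full placebo pooling loses nothing.
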